### Quantitative Measures

We will collect measures as outlined in Table 4 for both C3Link Core and C3Link Plus strategies.

**Table 4. T4:** Implementation outcomes measurement.

Constructs	Measures	Stakeholder and data	Frequency
Acceptability, feasibility, and appropriateness	AIM^a^, FIM^b^, and IAM^c^ 4-item measures	Women, family, study CHW, and clinic team surveys	24- and 36-month follow-up
Fidelity^d^ (group education, clinic team meetings, and individual strategies)	All content or topics are delivered, and sessions and meetings take place in the frequency and sequence planned	Study CHW tracking tool and clinic meeting minutes	12, 24, and 36 months
Sustainability	SMSS^e^ subscales specific to strategies	Study CHW and clinic team survey	24 and 36 months

a AIM: Acceptability of Intervention Measure.

b FIM: Feasibility of Intervention Measure.

c IAM: Intervention Appropriateness Measure.

d Dose is also included, and details are provided in Tables2  3.

e SMSS: Sustainment Measurement System Scale.

Our measurement will include the 4-item questions from each of the Acceptability of Intervention Measure, Feasibility of Intervention Measure, and Intervention Appropriateness Measure [72]. We will collect implementation feedback from C3Link CHWs and clinic teams participating in team meetings. The fidelity measures described in Table 4 will be compiled annually throughout this study’s implementation, and summary statistics will be generated to assess compliance with study protocols. Sustainability will be assessed using subscales of the Sustainment Measurement System Scale [73] applicable to the CLink package of strategies.

### Qualitative Feedback

We plan to conduct interviews and focus groups to identify underlying moderating factors associated with the successful implementation of strategies, along with facilitators and barriers to inform future scale-up activities. First, at the end of the intervention implementation phase (24 months), trained data collectors will interview all 18 study CHWs from the C3Link Core and Plus communities and 6 clinic team members participating in C3Link implementation activities in each of the 9 clinics. These 18 CHWs are the total number of C3Link CHWs, where 9 are from the C3Link Core arm, and 9 are from the C3Link Plus arm. These CHWs will be distributed equally among the 3 counties—6 per county. We anticipate that differences and similarities will be based on study arm, county, or on the different iterations of the 2 variables. Categorization by study arm, by county, and by the different iterations may enrich the stories, but data saturation may be compromised. This may be reduced by the fact that participants will be information-rich, having been involved in the implementation continuously for over a year. We will develop an interview guide with questions and probes to seek feedback from study CHWs and clinical teams on their level of preparedness to implement the strategies, their assessment of the quality of the delivery, and the level of responsiveness of the target groups. We will also pose open-ended questions to determine what they felt were facilitators to deliver the strategies and potential barriers. In follow-up questions, we will explore suggestions to address the barriers.

Second, at the end of the maintenance phase (36 months), the research team will conduct 6 focus groups with C3Link CHWs and clinic teams that were interviewed (2 focus groups per county). These focus groups will explore topics related to the sustainability of the package of strategies, drawing on the findings from the Sustainment Measurement System Scale survey results. The focus group setting will allow for discussion among these key stakeholders and offer concrete feedback for future implementation in terms of best practices to further optimize the delivery of the strategies. To facilitate analysis, all interviews and focus groups will be transcribed and translated with supervision from the Kenya grant implementation team and stored in secure servers.

### Qualitative Data Analysis

Using coding reliability thematic analysis [74,75] and keeping an audit trail of coding decisions and theme development, 2 grant analysts will independently review the transcripts to develop the initial codebook. Transcripts will be coded and key themes derived using qualitative software such as NVivo (Lumivero). An iterative process of rereading the transcripts may identify new codes, and the codebook will be modified accordingly. All investigators will critically discuss interpretations of the data, with focus on accuracy and consistency, until they reach a consensus on the dominant themes and meanings, minimizing analysts’ subjectivity and bias that is based on their own background and understanding, as would be seen in reflexive thematic analysis [74]. Important excerpts will be included in reports and publications. Qualitative findings will offer insights into differences in the delivery of strategies in the C3Link Core and Plus arms.

### Triangulation of Findings

We will compare the quantitative data with the qualitative findings to identify areas of convergence and divergence. The study team will review the tabulated data on the implementation outcomes with the key themes drawn from the interviews and focus groups with study CHWs and the clinic team members. Areas of agreement will be highlighted, and we will use the qualitative data to provide additional nuanced context for the quantitative findings. When we identify discrepancies between the quantitative data and qualitative feedback, the study team will use reflective thinking based on learnings gained during the course of implementing the interventions to understand reasons for the variation. We will also discuss these findings with study counties to gain additional insights and to derive actionable findings for future implementation.

### Cost-Effectiveness and Return on Investment Analysis to Support Scale-Up of Effective Approaches and Implementation Strategies

The objectives of this analysis are the following: (1) to assess the short-term cost-effectiveness of C3Link Core and Plus strategies by conducting a comparative cost-effectiveness analysis across the trial arms and (2) to project the long-term cost-effectiveness of integrated approaches to promote breast and cervical cancer screenings. We will use a customized 3-step process to address these objectives.

### Step 1: Short-Term Cost-Effectiveness Analysis

As presented in Table 5, we will collect detailed cost data, and for the planned short-term analysis, we will generate the cost of start-up activities to understand the resources required to plan future implementation and the activity-based cost of strategies during the intervention and maintenance phases. We will use a previously validated instrument, the Cost Assessment Tool [76], to collect resource use and cost information. Our main goal is to estimate the implementation cost from the program perspective. We will estimate labor hours and document the expenditures on nonlabor resources to host trainings and women’s club and family education sessions, the cost of addressing barriers identified in C3Link Plus navigation services, and costs borne by women to undertake screenings. Based on these cost estimates and the screening completion end points, we will conduct an incremental cost-effectiveness analysis by generating the cost per woman screened. Using standard economics methodology [77,78], we will explore economies of scale related to implementation costs that can be achieved during scale-up.

**Table 5. T5:** Cost data collection and analysis by phase.

Phase	Data category	Purpose	Data elements (examples)
Preimplementation phase	Start-up costs	To assess the cost of planning to implement strategies	Formalizing plans for the intervention; hiring staff; conducting training, needs assessment, and capacity building
Intervention and maintenance phases	Implementation of activity-based cost data	To assess the cost of implementing and maintaining interventions	Implementation activities: delivering strategies; tracking outcomes, quality assurance, data collection, and evaluation Patient cost: travel cost, time lost from work
Intervention and maintenance phases	Resource use	To standardize cost	Labor hours (study CHWs^a^ and clinic teams), nonlabor resources
Future expansion phase	Scale-up cost	To estimate the cost of large-scale implementation	Fixed vs variable activity-based cost estimates of implementation strategies to project economies of scale

a CHW: community health worker.

### Step 2: Cohort-Based Microsimulation Modeling for Breast and Cervical Cancer Separately

The screening effectiveness data and information on the use of services along the cancer care continuum from each of the trial arms will be used as inputs in previously validated breast and cervical cancer screening lifetime simulation models developed by RTI [79-81].

These models will be recalibrated with up-to-date input data from Kenya, including mortality and treatment survival statistics, and external validation will be conducted by comparing the outputs of the models (not including any interventions) with the current Kenyan stage at diagnosis and cancer incidence. We will conduct extensive sensitivity and uncertainty analysis to offer insights into likely real-world impacts [82]. The model results per 100,000 women will be used to compare differences across the enhanced standard of care, C3Link Core, and C3Link Plus. We will also generate cancer and mortality incidence rates under various screening scenarios in 5-year age increments for each trial arm.

### Step 3: Population-Level Simulation of the Impacts of Integrated Breast and Cervical Cancer Screenings

We will use data from the Kenyan census and the outputs from the microsimulation models to conduct population-level simulations of the joint impacts, considering both effectiveness and cost, of integrated promotion of breast and cervical cancer screenings. The cost information related to the integrated implementation of strategies for breast and cervical cancer screening from step 1, along with the cost of the screening tests, supplemental and diagnostic procedures, and cancer treatment from a recent publication by the research team [82], will be used to generate cost-effectiveness estimates. Our estimates will include both direct and indirect costs. In addition to the comparison across scenarios, we will compare the integrated promotion of breast and cervical cancer screening to the comparator of stand-alone screening programs for which we will derive projected cost and effectiveness data from published studies [62,83-85], to conduct scenario analysis. We will evaluate the trade-off, or return on investment, between the strategies used in each arm of the trial and report the projected decrease in cancer incidence and mortality under each set of strategies. We will conduct policy simulations to assess the impact of scaling up the interventions, perform sensitivity analysis, and generate potential best- and worst-case projections. This cost-effectiveness analysis will be complemented by a budget analysis, which will identify the financial outlays for the integrated strategies that will be required annually to implement the C3Link Core and C3Link Plus during various phases in the scale-up process.

### Ethical Considerations

This study is registered on ClinicalTrials.gov (NCT06572774), and deidentified data from this study (with consent from participants) will be updated within the registered trial. This protocol was reviewed and approved by the RTI (TUDY00022177) and Strathmore University Institutional Scientific and Ethical Review Committee (SU-ISERC1754/23), independent institutional review boards (IRBs), with plans to communicate any protocol amendments to them for approval.

Study staff were responsible for obtaining written informed consent from all participants. Before implementation, all informed consent forms in all study languages (English, Kiswahili, Kamba, Kikuyu, and Kalenjin) were approved by this study’s IRBs. In Kenya, the legal age for consent for health research is 18 years. A travel and snack compensation of 500.00 Kenya shillings (US $3.89) will be offered to women participating in the RCT, and 1000.00 Kenya shillings (US $7.78) will be offered to women participating in the pretesting of education materials and pilot testing screening procedures.

While many of the data collectors have previous research experience, they will undergo a 3-day training program on study procedures, data collection, and research ethics before the start of participant interaction, consent, and data collection activities.

In addition to study staff, we will establish a Data Safety Monitoring Board–independent from the sponsor and funder for quarterly monitoring meetings, which includes 3 Kenyan experts (an academic, a clinician, and a civil society representative) working on women’s cancer screening and care.

## Results

This study was funded in July 2022. IRB approvals were in November 2022 (RTI IRB) and in June 2023 (Strathmore University–Institutional Scientific and Ethical Review Committee IRB). This study was registered on ClinicalTrials.gov in August 2024. Recruitment of this study’s cohort began in September 2024 and was concluded in December 2024. For timeline context, the cohort will be followed for 36 months, and data will be collected annually. Our primary end point analysis related to screening uptake and follow-up diagnostic test completion will occur after the collection of our 24-month data collection (in early 2027). We are conducting ongoing fidelity assessments of our interventions and reviewing the quality of data as we progress with this study’s implementation. We will host multiple forums with policymakers at the MOH, The National Cancer Institute of Kenya, and the counties. The head of NCI Kenya will serve as a key liaison to disseminate findings. The results of all analyses will be reported in separate manuscripts.

## Discussion

### Defining Features of our Approach

We will assess the effectiveness and cost-effectiveness of multicomponent behavioral strategies to increase the uptake of breast and cervical cancer screening and completion of recommended diagnostic and treatment services of the C3Link program conducted in 3 counties in Kenya. Our strategies, including CHW-led group education sessions for behavior change [86,87] and practice facilitation at clinics [88], have been shown to increase screening uptake and recommended follow-up procedures among populations. The varied intensity of our implementation strategies with sequential increments allows for an efficient process to identify a combination of implementation strategies with available resource-based guidance, which addresses a key constraint in implementing strategies in low- and middle-income countries.

This is a novel approach to conduct a systematic economic evaluation of integrated strategies and delivery of screening to support scale-up. Currently, there is limited evidence on the cost, cost drivers, and cost-effectiveness of integrated promotion of strategies to increase screenings. Integration can potentially be more cost-efficient than siloed approaches, but policymakers need evidence to make informed decisions. We will use a 3-step process that will begin with the assessment of the short-term cost-effectiveness of the 2 C3Link packages of strategies investigated in the cluster randomized trial, followed by cohort-based microsimulation modeling of the long-term impacts on incidence and mortality generated separately for breast and cervical cancers using existing models designed by the grant team [79-81]. Finally, we generate population-level projections of the budget impact and mortality reduction of integrated screenings.

We will create and maximize unique partnerships for sustainability, with stakeholder engagement and evidence from previous studies to co-design, plan, implement, and evaluate the C3Link strategies. We will work with county teams at each step of this study to ensure continual collaboration and community participatory approaches. Our goal is to develop county-level research and implementation capacity to strengthen cancer screening delivery beyond the grant period. Partnerships with governmental and community stakeholders promote adaptation, uptake, scalability, and sustainability of evidence-based interventions [89].

Although cluster randomization reduces contamination across study arms, it increases the risk that women in each arm may differ at baseline. This study’s sampling frame will allow us to assess baseline differences before randomization and adjust our sampling process with propensity score weighting methods. Second, data could be missing because of nonresponse and study attrition. This study’s CHWs in each community will maintain regular contact with the women, and we will also use rigorous field data collection practices, including training data collectors, developing protocols, and monitoring fidelity continually. To limit missing data, we will train clinic staff and data collectors and implement continuous quality review. Furthermore, we will address any missing data by including demographic covariates that will serve as proxies for dropout and conducting sensitivity analyses.

We will select 1 eligible woman from within each household in the selected communities. To reduce interviewer bias, we will use the Kish method to provide a random and consistent procedure for women’s selection.

A key constraint in implementing strategies in low- and middle-income countries is funding. This is the first cancer screening study in Kenya, and to our knowledge, in any other limited-resource setting, that will evaluate implementation strategies in a predetermined sequence and assess effectiveness and cost at each step. This will allow us to determine the incremental cost-effectiveness of each strategy in the sequence to guide policy. For example, given the available resources and cost-effectiveness profile, a Kenyan county may decide to implement C3Link Core with only the first level in the sequence of C3Link Plus. Importantly, the findings will guide future studies in testing additional combinations and sequences.

This trial features novel evidence-based strategies to increase uptake of breast and cervical cancer screening in variously resourced settings in a cost-effective process. We anticipate that the findings will be valuable not only in Kenya but also in other sub-Saharan African countries.

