### Implementation Strategies

Women enrolled in the C3Link Core and Plus communities will receive a package of strategies delivered by study CHWs in the community setting. CHWs are community members who receive standardized training to collect data on demographics and health needs in their communities while supporting management of minor ailments and making referrals for other ailments. Each CHW supports up to 100 households. In Kenya, they are referred to as community health promoters.

CHWs play an important role in addressing individual and interpersonal barriers to improve knowledge and encourage women to seek medical care. In order to optimize available resources, we will adopt a tiered process through which only women who require multiple strategies are offered them. We will include a C3Link Core group receiving education sessions only where CHWs deliver group education sessions to women and their support persons, a C3Link Plus group will receive the C3Link Core group education sessions and later add on individual evidence-based strategies that increase in resource intensity in a sequential order, targeting women who remain unscreened at 1-month intervals, and a third group receiving enhanced usual care (ie, distribution of flyers in addition to usual care).

At the clinic level, C3Link Core and Plus strategies will use practice facilitation in clinics to foster team-based care with CHWs embedded within the clinic teams to build optimal community linkages and communication channels. CHWs serving as team members in the clinic setting can cocreate optimal processes in screening clinics to coordinate the return of test results to women and support completion of follow-up recommendations. We will provide education to health care providers to improve communication and reduce any stigmatizing behaviors. Through the practice facilitation process, we will implement a learning collaborative that offers peer-to-peer consultations to improve screening capacity.

The enhanced standard-of-care communities will not have any CHWs. During enrollment, we will distribute campaign flyers provided by the National Cancer Institute of Kenya. Women who visit clinics may benefit from quality improvement processes. Table 1 provides details on the activities and goals of strategies during each phase of this study.

**Table 1. T1:** Training and delivery of the multicomponent strategies.

Setting—Goal	C3Link^a^ Core and C3Link Plus	Enhanced standard of care

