### C3Link Community Implementation

We will recruit C3Link study CHWs (women) from the C3Link communities in the preimplementation phase using the same process used by the Kenyan counties. We will assign 1 study CHW in each community selected to implement C3Link Core or Plus strategies. To ensure continuity, the study CHW will have the primary responsibility for the implementation and will be supported by county CHWs who will step in if required. The study CHWs will receive a 1-week training session that will be delivered by our study team. They will receive training on 13 standardized topics, including practical experience providing services in the community. The study-specific topics will include breast and cervical cancer screening, review of the content of the education sessions for women and support persons, and facilitation of group education sessions. The C3Link Plus CHWs will later receive training on the facilitation of one-on-one education sessions, motivational interviewing techniques, and delivery of navigation services. The C3Link study-specific training content will be prepared by updating training materials (based on published toolkits) [49-53] developed by the team for ongoing studies (R01CA200845 and UH3HD096908). Study CHWs will also be trained in the use of the C3Link CHW tracking tool, in which they will be documenting all interactions with the participants.

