### Recruitment

The 3 communities per study clinic will be randomly assigned to one of the following study arms: C3Link Core, C3Link Plus, or enhanced standard of care. Trained study data collectors and study CHWs will visit households in the selected communities with the help of county CHWs (promoters). They will visit households in selected communities and enroll eligible women. Women will be eligible to participate if they are 30 to 55 years of age to capture most cases of persistent HPV infections (lower age limit) and those within the peak age groups of breast cancer incidence rate in Kenya (higher age limit). These women will be due to receive both breast and cervical cancer screening during this study’s intervention phase based on Kenyan guideline recommendations, not experiencing breast or cervical cancer symptoms, not pregnant, fluent in a study language (English, Kiswahili, Kamba, Kalenjin, and Kikuyu), and have plans to remain in the community for at least 2 years. We will include women who meet the inclusion criteria (1 per household using the Kish method) [65].

The study CHWs will administer a short survey to all women to assess eligibility for this study. The data collectors will administer the baseline survey to women who will give voluntary informed consent to participate. Each enrolled woman will be allowed to select a support person (spouse or community member) older than 18 years of age—the legal age for consent for health research in Kenya, with help from their CHW if needed. Selecting a support person will be voluntary. Study CHWs will administer a support person eligibility checklist tool before data collectors administer the support person baseline survey to those who give voluntary informed consent.

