### Data Collection

To assess the impact of the C3Link Core and Plus strategies on the mediating outcomes, we will conduct surveys to collect data from women, support persons, and providers in the clinics. Study CHWs will document strategy implementation in the C3Link CHW tracking tool, and this information will be used to determine the “dose of the intervention” (ie, in the community setting, dose is the number of education sessions attended or the type of individual-level intervention). We will track all health care service use of women enrolled in this study by conducting clinic audits at all 9 clinics and referral facilities. Data will be collected using tablets, which will contain REDCap (Research Electronic Data Capture; Vanderbilt University) programs to collect and store the data. Deidentified data will be transferred and stored in secure, password-protected servers. Research Triangle Institute (RTI) and Implenomics staff will conduct further data quality review, produce reports, and develop analytic files for collaborative analysis. Tables2  3 present end point definitions and biological, imaging, self-report, and clinic audit data collected at baseline and to be collected at 12-, 24-, and 36-month follow-ups.

**Table 2. T2:** Data collection at baseline, 12 months, 24 months, and 36 months. Data elements for primary, secondary, and follow-up end points—cancer care continuum.

Constructs or measures	Instrument and specification	Source	Timing
Proportion of women undergoing recommended cancer screening (primary end point measured at 24 months)	Cervical: Papanicolaou test (cytology laboratory), HPV^a^ DNA (Roche Cobas platform or Cepheid GeneXpert); breast: CBE^b^ or mammograms	Biological, imaging, and clinical procedures identified through clinic audits and this study’s database	12, 24, and 36 months
Proportion completing supplemental and diagnostic procedures in ≤90 days	Measured as days from referral to undergo procedures such as ultrasound, biopsy, colposcopy, and ablation of cervical lesions	Biological, imaging, and clinical procedures identified through clinic audits and this study’s database	24 and 36 months
Proportion of patients with cancer diagnosis initiating treatment in ≤90 days	Measured as days from cancer diagnosis to start of treatment; prespecified abstraction tool to identify dates and procedures	Biological, imaging, and clinical procedures identified through clinic audits and this study’s database	24 and 36 months

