Quality of screenings and communication of findings	Number of inadequate cervical samples (self and provider collected); proportion of mammography reports with breast density; percent test results shared with women within 2 weeks	Clinic audit, study CHW tool, and study database	Monthly
Screening for breast and cervical cancer	Number and type of tests; proportion of women receiving the test	Clinic audit, study CHW tool, and study database	12, 24, and 36 months
Additional procedures by screen type	Number of supplemental and diagnostic tests conducted	Clinic audit, study CHW tool, and study database	12, 24, and 36 months

a RTI: Research Triangle Institute.

b CHW: community health worker.

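### Retention contact, and possibly some screening capture, depends on study community health workers (CHWs) who work only in Core and Plus; the plan does not limit the primary end point to sources shared by all arms

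*Protocol article*

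**What the plan says.** On retention, the Discussion (Defining Features of our Approach) acknowledges nonresponse and attrition and answers first that the study's "CHWs in each community will maintain regular contact with the women". It adds field training, fidelity monitoring, quality review, demographic covariates as proxies for dropout, and sensitivity analyses.

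On where study CHWs work, four places agree. Implementation Strategies: "The enhanced standard-of-care communities will not have any CHWs". Table 1 shows no study CHWs in the control column. C3Link Community Implementation: "We will assign 1 study CHW in each community selected to implement C3Link Core or Plus strategies". Qualitative Feedback counts 18 in total, "where 9 are from the C3Link Core arm, and 9 are from the C3Link Plus arm".

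On outcome sources, the Table 2 row for the primary end point refers to biological, imaging and "clinical procedures identified through clinic audits", together with the study's database. The Table 3 row on breast and cervical screening gives its source as "Clinic audit, study CHW tool, and study database". The CHW tracking tool is described under C3Link Community Implementation, where CHWs are trained in its use and "they will be documenting all interactions with the participants".

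**The concern.** Two procedures that should be the same in every arm lean on staff who are themselves part of the intervention.

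The first is retention. A contact procedure described as universal cannot operate in a third of the communities, and that third is the whole control arm. Survey follow-up at 12, 24 and 36 months could therefore differ by arm. This bears mainly on the self-reported mediators: self-efficacy, social support, stigma and knowledge of risk.

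The second is outcome capture. Study CHWs are well placed to learn who has been screened. They tell women when HPV results are ready and contact those who do not attend, and in Plus each woman's screening status must be known at 9, 10 and 11 months to trigger the next step. If such knowledge enters the study database and counts towards the end point, a screen that the facility audits miss can be found in Core or Plus but not in control. Intent-to-treat analysis keeps women in their allocated arm but does not equalise detection, and demographic covariates do not describe an arm-specific source of information.

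**Working it through.** **Location of the safeguard.** Communities: 9 clinics × 3 = 27. Study CHWs: 9 (Core) + 9 (Plus) + 0 (control) = 18. Communities without the named retention contact: 27 − 18 = 9, all control.

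**The plan's own power figure.** Inputs from Study Design and Sample Size Determination: 9 communities of 100 women per arm, attrition up to 20% (so m = 80), ICC 0.03 to 0.05, two-sided alpha 0.05, 15% against 30%.
- Design effect = 1 + (m − 1) × ICC: 1 + 79 × 0.03 = 3.37; 1 + 79 × 0.05 = 4.95.
- Effective n per arm = 720 / design effect: 213.6 and 145.5.
- Power: 96.3% and 86.9% (94.3% and 83.2% with a t distribution on 16 df).

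The stated power of over 80% reproduces. The calculation takes attrition and capture to be equal in all arms.

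**Effect of unequal capture.** The documents give no capture rate by arm, so this is an assumption: 100% capture in Core and Plus, and 90% or 80% in control. It supposes that CHWs recover every screen the audits miss, so it is an upper bound for the stated gap.

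Spurious difference = true uptake × (capture in intervention − capture in control).
- True uptake 15% in both arms: 0.15 × 0.10 = 1.5 points; 0.15 × 0.20 = 3 points. Against the 15-point target: 10% and 20%.
- True uptake 30% in both arms: 0.30 × 0.10 = 3 points; 0.30 × 0.20 = 6 points.
- Under the planned alternative (15% against 30%), observed control uptake would be 13.5% or 12%. The observed difference would be 16.5 or 18 points instead of 15, again an excess of 1.5 or 3 points.

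**Against sampling error.** At 15% uptake in both arms, SE = √(2 × 0.15 × 0.85 / n): √(0.255/213.6) = 3.5 points and √(0.255/145.5) = 4.2 points. The 1.5-3 points therefore equal about 0.4 to 0.9 SE.

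The probability of a two-sided rejection when true uptake is equal, from a two-proportion test on the effective n (a simple stand-in for the planned GEE), is nominally 5%. Ranges run from ICC 0.05 to 0.03:

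| True uptake, both arms | Control capture 90% | Control capture 80% |
|---|---|---|
| 15% | 6.5-7.3% | 11.6-14.8% |
| 30% | 8.7-10.5% | 21.0-28.7% |

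**Unequal loss.** If lost women were counted as unscreened and retention were 85% in intervention and 75% in control (assumed), the spurious difference would be 0.15 × 0.10 = 1.5 points at 15% uptake and 0.30 × 0.10 = 3 points at 30%. In a complete-case analysis the sign depends on who stays. If the control women who remain are the more engaged ones, observed control uptake rises and the bias runs against the intervention.

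**The case against.** The strongest reply is that the primary end point does not name the CHW tool. Table 2 cites audits and the study database. The tool appears in Table 3, among mediating outcomes, auxiliary end points and dose, and there it is listed separately from the database. The audits cover the nine study clinics and the referral facilities for all enrolled women. Each clinic serves communities from all three arms, so audit quality should be balanced within clinic. Communities are chosen close to the clinics, and nothing in the document shows material screening elsewhere. An audit also does not need survey contact: a woman lost to the surveys can still be found in the clinic record.

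All of this stands, and it limits the point to screens that the audits miss and to CHW entries that reach the database. It does not close it. Table 3's dose rows pair the CHW tool with the study database, and no sentence keeps CHW entries out of the Table 2 end point.

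On retention, the Discussion's wording might be shorthand for each community that has a study CHW. That would remove the contradiction but not the gap, because the named contact would still be missing in control. County CHWs helped with household visits at recruitment, but the document gives them no retention role in control communities.

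A reader might go further in three ways that the documents do not support. One is that unequal capture and unequal loss both favour the intervention; for loss, the direction depends on handling that the article does not fix. Another is that records are wrongly matched more often in control; nothing in the text bears on this. The third is that eligibility screening was biased because "The study CHWs will administer a short survey to all women to assess eligibility for this study". That concerns enrolment, not detection of screening, and enrolment has closed.

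**Conclusion.** The point holds as a risk that the plan leaves open, not as a demonstrated bias. What is certain is that the named retention safeguard cannot operate in 9 of 27 communities, and that one screening row relies on a source that cannot exist in control. What is possible is that the primary end point inherits that source through the study database.

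The size cannot be derived from the documents. Under the assumed 10-20% of screens found only through CHWs, it is 1.5-3 points at the planned 15% control uptake, or 10-20% of the target difference. The 3-6 points need 30% true uptake in both arms, twice the planned control figure, and should be read as a secondary scenario. It would be wrong to conclude that the primary result will be biased, since the audits are neutral between arms and may capture nearly everything. The change is still worth making, because it is cheap and the 24-month analysis is not due until early 2027.

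**What to change.** - State that the 24-month primary end point counts only screens documented in clinic and referral-facility audits, abstracted in the same way for all 27 communities and without knowledge of arm where feasible.
- Use the CHW tool for dose and fidelity only. Report screens known solely through CHWs separately, and amend the source in the Table 3 screening row to match.
- Correct the Discussion so that retention contact is one procedure available in all arms, carried out by the existing data collectors.
- Report loss to follow-up by arm.

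The cost is end-point wording, an extraction rule and some data-collector time for contact. The small downside is that a few true screens known only to CHWs would not count.
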